### Setting

The collaboration involves a large number of European centers, most of which are academic hospitals (Figure 1). Starting with the eight centers of the PrescrAIP core group, the study now encompasses centers in Germany (12), the United Kingdom (5), the Netherlands (3), Turkey (3), Italy (3), Spain (3), Norway (2), Poland (2), Russia (2), Hungary (2), Czech Republic (2), Lithuania (1), Ukraine (1), Denmark (1), Sweden (1), and France (1).

**Figure 1 F1:**
[figure not shown]
European centers (dots) involved in the PrescrAIP Study.

### Data Collection

Patient data will be collected from the hospitals' medical records. Variables were selected to answer the research questions and meet the objectives of the study. Variables will be recorded in a REDCap-based (https://www.project-redcap.org) electronic datasheet (electronic case record form, eCRF), hosted by The North Denmark Region. The principal investigator of each site will ensure that the data in the eCRF are accurate, complete and legible. REDCap is a secure, online application designed to support data acquisition and storage by providing a shapeable interface for validated data entry.

### Assessment Variables

At the time of inclusion, all relevant variables will be recorded in the eCRF. These will include variables on demography and epidemiology, disease characteristics (radiological, laboratory and clinical), the set of diagnostic criteria employed, treatment (type, dose, duration), and short and long-term clinical outcomes. The complete variable list and definitions are reported in Appendix 1. AIP subtypes will be defined following the analysis of the above-mentioned variables. Given that patients with elevated serum IgG4 but without other organ involvement or biopsy sample can potentially be misdiagnosed, a subgroup with these characteristics will be created. Then a sensitivity analysis with and without excluding this subgroup will be performed to evaluate potential differences in the outcomes.

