This project has several strengths. Based on a multicentre cohort, this pan-European AIP study will provide a large dataset, dealt by field experts. Indeed, the vast majority of AIP reports derive from North-American or Asian cohorts, with most likely distinct genetic or environmental features that might not be shared by European AIP patients. Therefore, our study will plausibly provide a more homogenous AIP population thus far not included in recent trials. Due to the rarity of AIP, multicentric collaboration offers the unique possibility of obtaining more reliable results since larger patients' cohort can be analyzed. Moreover, the electronic datasheet will guarantee data quality and safety and will also stimulate data homogeneity across the various very heterogeneous countries and practices.

The study does not come without limitations, it being a descriptive retrospective study. There is a risk of the clinical and diagnostic guidelines being applied differently throughout the recruitment period. To mitigate this, we have collected clinical symptoms, laboratory and radiological findings rather than using the derivative AIP subtyping of the clinician. For example, as in most institutions pancreatic biopsies are not performed, seronegative type 1 AIP confined to the pancreas could be misdiagnosed as type 2. Conversely, atypical type 2 AIP with elevation of serum IgG4 might be classified as type 1 AIP. By subgrouping patients according to clinical, histopathological (where available) and radiological findings we aim to better judge the AIP subtype of the patient we aim to better judge the AIP subtype of the patient and increase transparency and uniformity of the AIP diagnoses made. As the response to a steroid trial might in some cases establish the diagnosis of AIP incorrectly, we will perform a subgroup analysis in patients in whom the AIP diagnosis was based on the successful steroid trial. Hereby, we will be able to estimate the effect of this group on the overall results of our analysis. In addition, we will be enabled to perform sensitivity analyses in that distinct subgroups, as described above. Lastly, many patients have a long follow-up, which should strengthen the true AIP diagnosis.

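### The inputs to AIP subtype are worded to include treatment and outcomes, and the article does not limit them to findings made before relapse

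*Protocol article*

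**What the plan says.** Assessment Variables (Methods) describes the recording: "At the time of inclusion, all relevant variables will be recorded in the eCRF". The list covers demography, disease characteristics and the diagnostic criteria used, and closes with "treatment (type, dose, duration), and short and long-term clinical outcomes". After a pointer to definitions elsewhere ("The complete variable list and definitions are reported in Appendix 1"), the section gives the rule: "AIP subtypes will be defined following the analysis of the above-mentioned variables".

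The same section sets up a group of doubtful diagnoses: "patients with elevated serum IgG4 but without other organ involvement or biopsy sample can potentially be misdiagnosed, a subgroup with these characteristics will be created". Its purpose is then stated: "a sensitivity analysis with and without excluding this subgroup will be performed to evaluate potential differences in the outcomes".

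The Discussion describes subtyping more narrowly. It names symptoms, laboratory and imaging findings, and histology where there is any, and says that these replace the treating clinician's own subtype. It does not name treatment or relapse as inputs, and it gives no time window.

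Relapse and relapse-free survival are primary endpoints (Study Endpoints), and finding risk factors for relapse is a secondary objective (Objectives). Statistical Analysis plans log-rank comparisons between subgroups, a Cox model with backward selection for predictors of relapse, and sensitivity analyses with and without NOS-AIP patients.

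**The concern.** Read as written, the rule in Assessment Variables lets outcome data enter the definition of subtype, while relapse is the outcome to be predicted. The narrower account in the Discussion does not remove the difficulty, because a finding can be clinical, histological or radiological and still exist only because the patient relapsed.

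The design leaves room for this. Follow-up is already in the chart when the variables are recorded, and the clinician's subtype is deliberately set aside, so the study's own rule decides the class. The Discussion itself says that most institutions do not take pancreatic biopsies and that seronegative type 1 disease confined to the pancreas can pass for type 2. Such patients could be moved to type 1 by later organ involvement, a repeat IgG4 or a late biopsy, and a relapse is an obvious reason for that work-up. The same patient without a relapse would keep the first class.

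Two results are at stake. One is any association between subtype and relapse, which would be inflated or created by reverse causation. The other is the set of sensitivity analyses that exclude NOS-AIP or the uncertain subgroup. If relapsers leave those groups through later work-up, the patients excluded are disproportionately non-relapsers, and relapse in the remaining cohort is pushed upwards.

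**Working it through.** The article gives no sample size, event count or power for this point, so there is no figure of its own to reproduce. The check has a textual part and an illustration.

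**Text**

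| Question | Assessment Variables | Discussion |
|---|---|---|
| Inputs to subtype | All listed variables, treatment and outcomes included | Symptoms, laboratory, histology, imaging |
| Treatment or outcome named? | Yes, through the list | No |
| Time limit? | None stated | None stated |

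The uncertain subgroup rests on three features (elevated IgG4, no other organ involved, no biopsy), and none of them is dated.

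**Illustration 1: reclassification when subtype has no true effect**

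Inputs: 400 patients presenting as type 1 and 200 as non-type 1 (assumed). True relapse is 40% in both groups (assumed; the Introduction cites 30% to 50% within 1 year of remission). This gives 160 and 80 relapsers. A share f of the 80 non-type 1 relapsers is moved to type 1 on findings made at relapse (assumed), so m = 80 × f.

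Apparent relapse in type 1 = (160 + m)/(400 + m); in the others = (80 − m)/(200 − m).

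| f | Type 1 | Others | RR | Chi-square P |
|---|---|---|---|---|
| 0% | 160/400 = 40.0% | 80/200 = 40.0% | 1.00 | – |
| 5% | 164/404 = 40.6% | 76/196 = 38.8% | 1.05 | – |
| 10% | 168/408 = 41.2% | 72/192 = 37.5% | 1.10 | – |
| 20% | 176/416 = 42.3% | 64/184 = 34.8% | 1.22 | 0.083 |
| 30% | 184/424 = 43.4% | 56/176 = 31.8% | 1.36 | 0.008 |

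The type 1 column also shows the effect on an exclusion analysis. If the whole non-type 1 group were left out, relapse in the remainder would read 41.2% to 43.4% for f of 10% to 30%, where the truth is 40%. That is a shift of about 1 to 3 percentage points.

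**Illustration 2: a second set of assumptions**

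Let r be the true relapse risk in every class (30% or 50%, the ends of the cited range), s the share that is type 1 at baseline (50% or 70%, assumed) and q the share of other relapsers relabelled as type 1 (assumed).

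- p1 = (s·r + (1 − s)·r·q) / (s + (1 − s)·r·q)
- p2 = r·(1 − q) / (1 − r·q)
- Apparent hazard ratio = ln(1 − p1) / ln(1 − p2)

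Example with r = 0.30, s = 0.50, q = 0.20: p1 = 0.18/0.53 = 34.0%, p2 = 0.24/0.94 = 25.5%, hazard ratio 1.41.

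Over the four combinations of r and s, the apparent hazard ratio is:
- q = 0: 1.00
- q = 5%: 1.05 to 1.09
- q = 10%: 1.11 to 1.18
- q = 20%: 1.25 to 1.41
- q = 30%: 1.42 to 1.69

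With an assumed 500 patients and a two-sided 0.05 test, the chance of a falsely significant excess in type 1 is about 27% to 61% at q = 20%, and about 5% to 8% at q = 5%. Without relabelling it is 2.5% in that direction.

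**The case against.** The strongest reply is that the definitions sit in Appendix 1, which is not shown and may date IgG4, organ involvement and biopsy to diagnosis. That stands as a limit: the missing date is a fact about the article, not necessarily about the full plan. It does not dispose of the point, because the article states a rule here, the rule is wider than the Discussion's, and the two need aligning in any case.

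It can also be said that the back-reference is loose drafting. The list contains demography and drug dose, and nobody would suppose that dose separates type 1 from type 2. This is fair. A reader might infer that relapse is meant to decide subtype, but the article says so nowhere. The wording permits it, and the Discussion suggests otherwise.

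Three further inferences go beyond the text:

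- A reader might conclude that the uncertain subgroup is itself assigned from treatment and outcomes. It is defined only by IgG4, organ involvement and biopsy ("patients with elevated serum IgG4 but without other organ involvement or biopsy sample can potentially be misdiagnosed"). Its weakness is that these features are undated.
- The Discussion's remark "Lastly, many patients have a long follow-up, which should strengthen the true AIP diagnosis" might be taken as a plan to use follow-up for subtyping. It concerns whether the patient has AIP at all.
- A reader might state that subtype will falsely predict relapse. Subtype is not among the stratifiers in Statistical Analysis, and the Cox candidates are not listed. The Introduction cites more relapse in type 1 than in type 2, which makes its use likely but not stated. The regimen comparisons, as described, do not depend on subtype.

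Finally, a strict pre-treatment cut-off would clash with steroid response being part of the diagnostic criteria. This stands, and the remedy must allow for it. The steroid-trial sensitivity analyses already planned deal with diagnosis by treatment response; they do not deal with a class set by findings at relapse.

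**Conclusion.** The point holds as a defect in how the classification is fixed. Assessment Variables and the Discussion disagree on the inputs to subtype, and neither keeps information from a relapse out. Bias in a subtype–relapse association, and in the analyses that exclude NOS-AIP or the uncertain subgroup, is therefore possible; it is not shown to occur.

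Its size rests wholly on the share of non-type 1 relapsers who are reclassified, which the article does not give. At an assumed 10% to 30%, a true relative risk of 1.0 appears as about 1.1 to 1.4. In the 400/200 example only the 30% case crosses the 0.05 threshold. At 5% the bias is small. The group sizes are also assumptions; only the relapse range of 30% to 50% comes from the article. The change is worth making because it is cheap and guards against reverse causation in a stated objective. If Appendix 1 already dates the variables, what remains is to bring the wording into line with it.

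**What to change.** 1. Reconcile Assessment Variables, the Discussion and Appendix 1 on the inputs to subtype. Remove treatment and outcomes from them, except steroid-trial response where the diagnostic criteria use it; the planned steroid-trial sensitivity analysis already covers that exception.
2. For all relapse, risk-factor and sensitivity analyses, assign subtype (including NOS-AIP) and the uncertain elevated-IgG4 subgroup from findings dated at diagnosis or start of first treatment, and never from findings at or after relapse.
3. Report a final subtype that uses all available information, for description only.

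The cost is some wording and the dating of three items (IgG4, organ involvement, biopsy) against diagnosis or start of first treatment. The downside is that more patients will be classed as NOS-AIP at baseline.

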### Study Endpoints

Our primary endpoints consist of remission of disease (defined as the absence of clinical symptoms and the resolution of pancreatic abnormalities on imaging), relapse of disease, relapse rates compared between patients with a low or a high dose regimen, cumulative maintenance therapy dose and relapse-free survival time. Our secondary study endpoints are gold standard diagnostic tools of AIP compared to U-AIP, the prevalence of pancreatic exocrine insufficiency and the cumulative incidence of pancreatic ductal adenocarcinoma. The diagnosis of diabetes mellitus [as defined by the American Diabetes Association (27)] either before or after steroid treatment is our tertiary study endpoint.

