## Abstract

**Introduction:** Treatment of autoimmune pancreatitis (AIP) is based solely on consensus and has yet to become standardized. Consequently, therapeutic regimens vary greatly between countries and centers, and largely depend on the experience of the physician. At this moment, the optimal regimen for inducing disease remission and preventing relapse is unknown.

**Objectives:** The primary objective of this study is to describe current treatment regimens used in Europe, and to compare their effectiveness in inducing remission and preventing and treating relapse. The secondary objectives are: to identify risk factors for relapse; to assess the diagnostic accuracy of the Unified-AIP criteria; to assess the performance of the M-ANNHEIM score for predicting relapse; and to assess long-term outcomes including pancreatic exocrine insufficiency and pancreatic cancer.

**Methods:** This is an international, retrospective, observational cohort study, performed in over 40 centers from 16 European countries. Eligible are all patients diagnosed with AIP from 2005 onwards, regardless of the used diagnostic criteria. Data on study subjects will be retrieved from the hospital's electronic medical records and registered with a standardized, web-based, electronic case report form (eCRF). To compare the effectiveness of treatment regimens in inducing remission, preventing relapse, and treating relapse, subjects will be stratified in groups based on: type of therapy; initial therapy dose; cumulative therapy dose; therapy tapering speed and duration; and having received maintenance therapy or not.

**Ethics and Dissemination:** Ethical and/or institutional review board approvals are obtained by all participating centers according to local regulations. The study complies with the General Data Protection Regulation (GDPR). All manuscripts resulting from the study will be submitted to peer-reviewed journals.

**Conclusion:** This is the first pan-European retrospective registry for AIP. It will produce the first large-scale data on treatment of European patients with AIP, providing answers on the use and effectiveness of treatment regimens. In the future, this collaboration may provide a network for continuation into a prospective European registry.

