## Methods

### Study Design

This is an international, retrospective, observational cohort study including all AIP patients. We used the Pancreas2000 framework (www.pancreas2000.org) to create a study network starting with the six centers in the PrescrAIP core group. Additional European centers with expertise in the treatment of AIP patients have been recruited, accumulating to a total of 44 collaborating centers.

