### Study Population

Every patient with an AIP diagnosis (type 1, type 2 or NOS-AIP) will be included, regardless of diagnostic criteria used (U-AIP, HISORt, ICDC). Patients with AIP diagnosed prior to 2005 will be excluded due to lack of uniformity in diagnostic standards.

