### Statistical Analysis

Continuous, non-normally distributed values will be presented as median and interquartile range (IQR), unless otherwise specified. Discrete variables will be presented as frequency (percentage). Normal distribution of continuous variables will be assessed with the Kolmogorov–Smirnov algorithm. Normally distributed variables among the different groups will be compared using the Student's *t*-test. Non-normally distributed variables will be compared using the Mann–Whitney *U*-test. Categorical variables will be analyzed by the Fisher's exact test or chi-square test.

To compare remission rates, relapse rates, relapse-free survival and long-term outcomes between participants, we will stratify participants according to the date of diagnosis, meeting the different diagnostic criteria, the type of treatment, the glucocorticoids starting dose, the cumulative dose, tapering speed, and treatment with maintenance treatment.

Moreover, to assess the impact of the treatment effect being part of the diagnostic criteria, we will perform sensitivity analyses comparing the study outcomes between those classified as AIP regardless of the steroid trial, and those in whom the diagnosis was dependent on the steroid trial. Sensitivity analyses will also be performed to compare the study outcomes including or excluding individuals that do not meet any available diagnostic criteria, and those classified as NOS-AIP.

Kaplan-Meier curves will be used to assess time-to-relapse. Time-to-relapse will be compared between subgroups using the log-rank test. Univariable and multivariable analyses with a backward selection procedure will be performed to identify possible predictors for relapse, based on a Cox-proportional hazards regression model. A significance threshold of *P* < 0.05 will be used.

Data from national pancreatic cancer registries will be used to determine age- and sex-specific incidence rates for pancreatic ductal adenocarcinoma. Standardized incidence ratios (SIRs) will be then calculated by obtaining the ratio of the observed to the expected number of cases, and 95% confidence intervals (95% CIs).

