## Ethics and Disseminations

This study was reviewed and approved by the ethics committees of the centers in the PrescrAIP core group, namely those at the San Raffaele Scientific Institute (Milan, Italy), the South East Regional Committee for Medical and Health Research Ethics (Oslo, Norway), the Erasmus University Medical Center (Rotterdam, The Netherlands), the Aalborg University Hospital (Aalborg, Denmark), the Marmara University School of Medicine (Istanbul, Turkey), the Institute for Clinical and Experimental Medicine (Prague, Czech Republic), the Karolinska University Hospital (Stockholm, Sweden), and the Martin Luther University Halle-Wittenberg (Halle, Germany). In addition, participating centers had the protocol reviewed and approved wherever required by local regulations.

Patients' data will be collected retrospectively from pre-existing electronic patient records. Study data will then be collected and managed using a REDCap database hosted at Aalborg University Hospital, North Denmark Region, Denmark. All data will be coded (pseudonymized). The key to the coded data will be stored locally in the participating site, in a password-protected file controlled by the Principal Investigator, and separately from any research data. For the German centers data will be anonymized immediately. When data is exported from the REDCap system for analysis, the data will be made completely unidentifiable and potential identifier variables will be removed. Additional processing of already collected data for the purpose of scientific research is exempt from specific consent according to Articles 5(1)(b) and 89(1) of the General Data Protection Regulation (GDPR). The study adheres to the Declaration of Helsinki. No patient will be exposed to any inconvenience in relation to the present study because all data are obtained retrospectively. The findings of the study will be published in a peer-reviewed journal and disseminated at national and international conferences.

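### Remission needs a scan but failure does not, and no scan is scheduled, so remission rates by regimen can partly reflect who was re-imaged

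*Protocol article*

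**What the plan says.** All references are to the Protocol article.

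- **Endpoint.** Study Endpoints lists remission among the primary endpoints and defines it as "the absence of clinical symptoms and the resolution of pancreatic abnormalities on imaging". The two conditions are joined, so both must hold.
- **Data source.** Study Design states: "This is an international, retrospective, observational cohort study including all AIP patients". Data Collection adds: "Patient data will be collected from the hospitals' medical records". Ethics and Disseminations confirms it: "Patients' data will be collected retrospectively from pre-existing electronic patient records". The study itself therefore schedules no imaging, and Study Population does not make follow-up imaging a condition of inclusion.
- **Centres and regimens.** The Abstract says that "therapeutic regimens vary greatly between countries and centers, and largely depend on the experience of the physician". Study Design describes recruitment "accumulating to a total of 44 collaborating centers". The Discussion acknowledges, in general terms only, that practice is very heterogeneous.
- **Comparison.** Statistical Analysis compares remission rates across strata of diagnosis date, diagnostic criteria met, treatment type, starting dose, cumulative dose, tapering speed and maintenance treatment. Centre and availability of follow-up imaging are not on that list. "Categorical variables will be analyzed by the Fisher's exact test or chi-square test". The Cox model is given for predictors of relapse.
- **Sensitivity analyses.** Those described in Assessment Variables and Statistical Analysis concern diagnosis: raised IgG4 without other organ involvement or biopsy, dependence on the steroid trial, patients meeting no criteria, and NOS-AIP. None concerns whether remission could be observed.
- **Definitions elsewhere.** Assessment Variables refers to Appendix 1 for the full list of variables and definitions. It is not shown.

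**The concern.** With routine records, the stated definition makes ascertainment one-sided. Consider three treated patients:

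- **A** is symptom-free and has a normal follow-up scan. A is in remission.
- **B** is symptom-free and was never re-scanned. The imaging condition cannot be shown, so B cannot be scored as in remission.
- **C** still has symptoms. C fails the definition whether or not a scan exists.

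Failure can be read from symptoms alone, but success needs a scan. How B is handled then matters. Counting B as a failure puts B with C. Leaving B out removes patients who are doing well, while C can stay in the denominator.

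Within one group this shifts the estimated remission rate. Between groups it matters if the share re-imaged differs by regimen. Regimens differ by country and centre, and re-imaging habits plausibly do too. A regimen favoured where well patients are seldom re-scanned would then look less effective. Comparing regimens in inducing remission is part of the primary objective, and no listed stratum or sensitivity analysis would separate the two explanations.

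**Working it through.** The article states no remission rate, re-imaging rate or sample size, so there is no figure to reproduce. The nearest is steroid response of up to 99% (Introduction), which is not remission as defined here. All rates and group sizes below are assumptions. The 0.05 threshold is from Statistical Analysis, and a two-sided test is assumed.

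**Illustration 1.** True remission is 95% under both regimens. Responders are re-imaged with probability f, non-responders with probability 0.95.

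- Unscanned counted as failures: observed remission = 0.95 × f.
- Unscanned left out: observed remission = 0.95f / (0.95f + 0.05 × 0.95) = 0.95f / (0.95f + 0.0475).

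| f | Unscanned = failure | Unscanned left out |
|---|---|---|
| 0.90 | 85.5% | 0.855/0.9025 = 94.7% |
| 0.80 | 76.0% | 0.760/0.8075 = 94.1% |
| 0.70 | 66.5% | 0.665/0.7125 = 93.3% |

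For 90% versus 80%, the spurious gap is 9.5 points if the unscanned are failures and about 0.6 points if they are left out. For 90% versus 70% it is 19 and about 1.4 points. With 100 patients per group and the unscanned as failures, a simulated chi-square test rejects in about 40% (90 v 80) and 90% (90 v 70) of studies, against 5% with equal re-imaging. With continuity correction the first two are 33% and 86%.

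**Illustration 2, separating the two conditions.** Let s = 0.90 be symptom-free and q = 0.90 of those have imaging resolution, so true remission is 0.90 × 0.90 = 81% in both groups. Symptom-free patients are re-imaged with probability f, symptomatic patients with g = 0.95.

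- (i) Unscanned as failures: sqf.
- (ii) Re-imaged patients only: sqf / (sf + (1−s)g).
- (iii) Unscanned symptom-free patients left out, all symptomatic patients counted as failures: sqf / (sf + (1−s)).

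| f | (i) | (ii) | (iii) |
|---|---|---|---|
| 0.90 | 72.9% | 80.6% | 80.1% |
| 0.80 | 64.8% | 79.5% | 79.0% |
| 0.60 | 48.6% | 76.5% | 75.9% |
| 0.30 | 24.3% | 66.6% | 65.7% |

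The approximate chance of P < 0.05 at 90% versus 60%, with 50, 100 and 200 patients per regimen, is 71%, 95% and over 99% under (i). Under (ii) or (iii) it is about 7%, 10% and 16–17%. These last figures use the full group size although patients are left out, so they are slightly generous. At 90% versus 80%, (i) gives about 14%, 23% and 42%; (ii) and (iii) show no material excess over 5%.

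**When leaving out also misleads.** With true remission 90%, responders re-imaged in 50% and non-responders in 95%, the estimate is 0.90 × 0.50 / (0.90 × 0.50 + 0.10 × 0.95) = 0.45/0.545 = 82.6%. This is bias in one group, not a difference between regimens, and it needs much lower re-imaging of responders.

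**When it hardly matters.** With s = 0.99 and q = 1, (ii) and (iii) stay at 97–99% for f from 0.3 to 1, while (i) falls to 29.7% at f = 0.3.

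**What bounds would show.** In Illustration 2, the symptom-free, not re-imaged category is s(1−f). Setting it to non-remission gives sqf; setting it to remission gives sqf + s(1−f).

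- f = 0.90: 72.9% to 72.9% + 9.0% = 81.9%.
- f = 0.60: 48.6% to 48.6% + 36.0% = 84.6%.

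The order of the two groups reverses between the bounds although true remission is equal. That is the dependence a reader should be able to see.

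**The case against.** The strongest reply is that this is really a missing rule. Study Endpoints gives a one-line definition, and an imaging window or a not-assessed category is the kind of detail an article leaves to Appendix 1 or an analysis plan, neither of which is shown. That stands as far as it goes: the absence of a rule from the article is not the point here. The one-sidedness follows from the definition and the data source that the article does state. Whatever rule Appendix 1 holds, a scan that was never taken cannot be recovered. Counting such patients as failures, leaving them out or assuming remission each carries its own dependence on who was scanned.

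A reader might also infer a bias of 9.5 to 19 points from the definition itself. The document does not support that. It does not say that a patient without a scan counts as not in remission, and the ordinary reading of an unobserved component is unknown. With the unscanned left out, the same inputs give only about 0.6 to 1.4 points.

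Nor does any section say that re-imaging differs by centre, is rare in well patients or follows regimen. The Abstract speaks of regimens, and the Discussion of heterogeneous practice only in general.

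Finally, it would be too strong to say that remission status can be scored only in re-imaged patients. Persisting symptoms settle non-remission without a scan.

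**Conclusion.** The concern holds in a limited form. The stated endpoint, applied to records without scheduled imaging, lets failure be scored from symptoms but success only with a scan, and none of the stated strata or sensitivity analyses addresses this. If re-imaging differs between regimens, the remission comparison is distorted.

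The size cannot be derived from the document. Under the assumed rates it is large if symptom-free patients without a scan count as failures. It is usually small, though not zero, if they are left out, and becomes material there only when re-imaging of responders is much lower. That re-imaging differs by centre is a plausible inference, not a documented fact. No figure in the article is wrong, and the point does not show that any regimen comparison will be misleading. It shows that the result can depend on a handling choice whose effect should be visible.

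**What to change.** - Report clinical remission (symptom resolution) in all treated patients with follow-up, alongside imaging-confirmed remission as now defined.
- Keep symptom-free, not re-imaged as its own category, not counted as failure.
- Tabulate the share re-imaged by regimen.
- Add a sensitivity analysis that sets this category first to remission and then to non-remission, and describe regimen differences that depend on the choice as uncertain.

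A stricter rule, allowing a claim only when a difference survives both bounds, would be a matter of preference and is not needed.

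The cost is analysis wording and one extra table. Assessment Variables already plans radiological, clinical and outcome data, but without Appendix 1 it cannot be confirmed that follow-up scans are recorded as such, so that should be checked. Clinical remission also depends on what the records hold. The bounds may be wide, and some remission comparisons may become inconclusive.
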